### Randomization and allocation concealment

For randomization and allocation concealment, a set of random numbers will be generated using computerized SAS block-randomization software (SAS® version 9.3, SAS Institute, Inc., Cary, NC, USA). Sealed, opaque assignment envelopes will be used for allocation concealment [16].

The primary data collected will be used to investigate the impact of expectations on the success of acupuncture treatment. Because participant expectations could affect treatment outcomes, each patient will be queried regarding their perception of acupuncture therapy prior to group allocation [17]: 'How much do you expect that the acupuncture treatment will relieve your dry eye symptoms?’ Participants will be asked to select one point on a 10-point Likert scale (0 not useful to 9 very useful).

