## Intervention

### Acupuncture plus usual care group

The acupuncture plus usual care group will be treated three times per week for four weeks. Each session of treatment will include the use of 17 acupuncture points (bilateral BL2, GB14, TE23, Ex1, ST1, GB20, LI4, and LI11, and single GV23). These will be localized according to the 'WHO Standard Acupuncture Point Location in the Western Pacific Region’ protocol [18]. Four experts in the field of alternative medicine who have trained for at least seven years and practiced for at least three years will perform these treatments using 0.20 mm × 30 mm disposable acupuncture needles (Dongbang Acupuncture Inc., Chungnam, Republic of Korea). The '*de-qi*’ sensation will be induced by twisting acupuncture, and the needles will be retained for 20 minutes before removal. The patients will be allowed to use any additional treatment for dry eye symptoms other than punctal plugs or punctal occlusion surgery. Patients will not be permitted to participate in any other regimen of acupuncture therapy. Any changes in medical history or vital signs and reports of adverse events will be recorded at every follow-up visit.

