### Adverse events

Adverse events are unexpected signs, symptoms or diseases encountered during the clinical trial, whether or not they are related to acupuncture treatment. Local, general, and psychological adverse events may be observed. Local symptoms may include continual swelling, redness and itching lasting ≥ three days, peripheral neuritis and hemorrhage, and bruises/pain lasting ≥ two weeks. Systemic symptoms include headaches lasting longer than three days and circulatory problems, including dizziness and palpitations. Psychological problems include hypersensitivity for over three days and anxiety or fear for over 60 hours. All unexpected responses related to acupuncture treatment will be recorded. In order to prevent bias, an expert panel of individuals who are not otherwise connected to this study will evaluate any report of an adverse event. Each report will include a description of any associated symptoms, including the date of onset, the duration, and the degree of severity (Spilker’s criteria [22]: 1 = mild, 2 = moderate and 3 = severe, the patient’s perception of a causal relationship with the treatment (1 = definitely related, 2 = probably related, 3 = possibly related, 4 = probably not related, 5 = definitely not related and 6 = unknown), acupuncture-related action (1 = no change, 2 = temporarily suspend, 3 = suspend), treatment of the adverse event and treatment results. If serious adverse events (SAE) occur, these will be related to the IRB; experimental treatments will be stopped immediately and appropriate treatments will be administered.

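### The only causality rating stated for adverse events is the patient's own, against an undivided treatment; the independent panel is given no stated causality rating

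*Protocol article*

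**What the plan says.** The Adverse events section of the protocol article covers events "whether or not they are related to acupuncture treatment", and adds that unexpected responses related to acupuncture will all be recorded. It then lists what a report holds: the symptoms, onset, duration, a three-grade severity, a causality item, the action taken on acupuncture, the treatment of the event and its result.

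The causality item is the "patient’s perception of a causal relationship with the treatment", graded "1 = definitely related, 2 = probably related, 3 = possibly related, 4 = probably not related, 5 = definitely not related and 6 = unknown". It is the only causality rating in the article.

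Just before that list, the section says that, to prevent bias, "an expert panel of individuals who are not otherwise connected to this study will evaluate any report of an adverse event".

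Two other places bear on how the rating will work. Under Randomization and allocation concealment, the article asks each patient how much relief they expect from acupuncture, with the reason "Because participant expectations could affect treatment outcomes". Under Acupuncture plus usual care group, it says: "The patients will be allowed to use any additional treatment for dry eye symptoms other than punctal plugs or punctal occlusion surgery". The Usual care control group section is equally open and names artificial tears, cyclosporine, corticosteroids and autologous serum among the permitted treatments.

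**The concern.** Judging whether an event was caused by the treatment is the part of adverse event reporting most open to opinion. Here the article names the rater, the object and the scale: the patient, the treatment, six grades. Patients know whether they were needled, and the plan itself takes their expectations seriously enough to measure them before allocation. The body that could give a less involved judgement exists already, but nothing is said about it rating causality.

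What is at stake is the safety reading of the pilot. The Abstract promises data on the safety of acupuncture as well as its effectiveness. Any statement that an event was or was not related to acupuncture needs a relatedness judgement, and the only one described is the patient's, made against an object that is not divided into acupuncture and the rest.

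**Working it through.** No formula applies. The article states no adverse event rate and no calculation on this point, so the check sets the provisions side by side.

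1. **Who rates.** The Adverse events section assigns the six-grade item to the patient. This is a stated choice, not a gap: rater, object and all six grades are spelled out. No investigator or panel causality rating appears.

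2. **Whether the rater is masked.** The Abstract and the Usual care control group section describe a control arm that receives usual care only. There is no sham needling, so patients in effect know their arm.

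3. **What is rated.** The term *the treatment* is not defined. There are two readings.
   - *Broad: whatever the patient receives.* In the acupuncture arm this is needling plus almost any drop, drug or supplement. An event from a drop and an event from a needle can carry the same grade.
   - *Narrow: acupuncture only.* The item then has no meaning for controls, and an event caused by a co-treatment has no place to be attributed in either arm.

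   Neither reading gives separate attribution to acupuncture and co-treatment. Attribution by the patient is not easy either: redness and itching stand among the possible local adverse events and also among the dry eye symptoms in Table 1.

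4. **What the panel does.** It evaluates any report, and its purpose is to prevent bias. The causality entry in the report it receives is the patient's. The section does not say that the panel makes its own causality rating, or which view prevails if the two differ.

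5. **Whether counting all events by arm would make attribution unnecessary.** The acupuncture arm attends 3 sessions a week × 4 weeks = 12 sessions. Controls are followed up every two weeks, so 4 ÷ 2 = 2 follow-up contacts over the same four weeks. Opportunities to report an event differ by 12 ÷ 2 = 6 to 1. A difference in all-cause counts could come partly from that, so attribution still matters.

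**The case against.** The case on the other side has real weight.

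- **The panel is a safeguard, and may already judge causality.** It sees every report, and the patient's view is one entry among several. The article condenses a fuller protocol in which the panel's remit may be set out. This stands: one cannot say that the panel does not rate causality. But the point does not rest on silence alone, since the article does positively assign its one causality scale to the patient.
- **No related-event rate is defined.** A reader might infer that the trial's acupuncture-related event rate will simply reflect belief. The documents do not support that. Neither Statistical analysis nor Adverse events defines such a rate, or says that the patient's grade decides it.
- **Nearby wording points to acupuncture.** The section speaks of acupuncture treatment, and the item next to the causality scale is the action taken on acupuncture. The narrow reading is therefore the more natural one. That weakens a claim that drug and needle events will be mixed, but the narrow reading has its own defect, shown above.
- **Direction.** A reader might infer that hopeful patients will deny needle harm and so bias attribution downward. Nothing supports this. The expectation question is about relief of symptoms, and misattribution can run either way.
- **Co-treatment information is collected.** Controls report drug changes at each visit, and all participants keep a treatment diary from visit 14. That is true, and useful to a panel, but it is not an attribution.

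Any figure for the number of miscoded events would be invented, because the article gives no event rates to start from.

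**Conclusion.** The point holds in a limited form. The one causality rating that the article states is the effectively unmasked patient's perception of a relation to an undivided treatment. It is open to belief in either direction and does not separate acupuncture from freely used co-treatment. The panel set up against bias evaluates each report but has no stated causality rating to give.

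The conclusion rests on two things: that the absence of a sham means patients know their arm, and that the article's description of the report is accurate as far as it goes. If the full protocol already gives the panel a causality rating that takes precedence, only the wording of the article and the division between acupuncture and co-treatment remain to be settled.

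The effect cannot be sized from the document. For an exploratory pilot with 20 patients per arm, the point is minor. It touches the safety description, not the primary outcome analysis.

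**What to change.** State in the Adverse events section that the existing panel assigns the causality rating used for reporting, on the same 1 to 6 scale. Have it give two ratings per event: one for acupuncture, marked not applicable in controls, and one for concomitant dry eye treatment. Keep the patient's perception on the form as a supplementary descriptive item.

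The cost is one added form item and slightly more panel work. No visit, measurement or aspect of patient care changes. The panel's judgement will not be free of error, since the nature of an event can reveal the arm, but it is less exposed to the patient's own hopes or fears about acupuncture.

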## Discussion

Approximately 95% of patients suffer from symptoms of dry eye after refractive surgery. These patients may attempt to alleviate their symptoms using artificial tears, punctal occlusion surgery and/or lifestyle modifications [6,23]. Dry eye symptoms after refractive surgery are most commonly caused by iatrogenic corneal nerve damage, which contributes to a loss of corneal sensation [24]. This decrease in sensitivity can result in tear film instability, reduced tear secretion, a decrease in the number of conjunctival goblet cells and/or an increase in tear osmolality. Furthermore, there is evidence that the use of a corneal flap with a superior hinge can decrease corneal sensitivity, potentially leading to a reduction in the blink rate [23].

Prior studies have shown that acupuncture can modulate the autonomic nervous system and immune system, which in turn can increase lacrimal secretion by stimulating lacrimal gland function [14,25-27]. No previous study has examined the effects of acupuncture in the treatment of dry eye syndrome following refractive surgery. This pilot study will show whether acupuncture is effective in the treatment of postoperative dry eye syndrome [9-14]. The results should allow us to evaluate the feasibility of an extensive clinical study and to predict the number of subjects necessary for sufficient power.

## Trial status

Patient recruitment began in January 2013 and will continue until December 2013.

## Abbreviations

ANCOVA: Analysis of covariance; TBUT: Tear film break-up time; IRB: Institutional review board; ITT: Intention to treat; LASEK: Laser-assisted subepithelial keratomileusis; LASIK: Laser *in situ* keratomileusis; LOCF: Last observation carried forward; NECA: The national evidence-based healthcare collaborating agency; OSDI: Ocular surface disease index; PRK: Photorefractive keratectomy; QOL: Quality of life; SAE: Serious adverse event; VAS: Visual analog scale.
